### Randomization

All eligible recruited patients will be randomly divided into two groups with a 1:1 ratio and blocks of four and six performed by the co-investigator through the randomization list (randomization.com). The randomization list will be kept in safe storage with the co-investigator responsible for the stimulation sessions. She will provide the allocation concealment assignment for the patients. No information about the assigned group will be given for the patient or to the research assessor.

### Blinding and allocation concealment

Both helmets, the active and the sham, are identical in size, color, and weight. The active helmet activates the red light when plugged; however, the sham helmet cannot provide visible light. The patient is not able to see the light and there is no hit during the active stimulation that can suggest the type of intervention. The unblinded investigator is the person in charge of performing the stimulation. Both assessor researcher and patient will be blind for the type of intervention.

During the study, telephone contact can be used to maintain patient adherence to the trial. This study involves the participation of a research committee not directly related to the allocation of the patients. They can remove the blinding if any relevant situation may rise involving any clinical condition, adverse event, or even abandonment of the patient.

### Safety considerations and adverse events

Phase 1 trials and animal studies showed evidence related to the safety of the LLLT [24, 26, 53]. Although there are few studies in clinical patients, no side effects were reported using photostimulation and LLLT [17, 22, 37, 38, 54–57]. For safety, the LLLT will be applied by a registered nurse or a trained clinician.

### Ethical approval and consent to participate

The protocol was approved by CONEP Resolution 466/2012, which regulates scientific research involving human beings in Brazil. It follows the ethical principles of Declaration of Helsinki for medical research involving human subjects.

### Statistical analysis

Intention-to-treat and per-protocol analyses will be performed for the primary and secondary outcomes. Missing data will be analyzed with regression imputation, considering the confounders (months of the trauma, years of age, schooling years, and depressive symptoms). Patients that did not receive 60% of the total stimulation will be considered non-adherent and analyzed as per-protocol.

Means and standard deviation will be used to represent data with normal distribution and medians and quartiles to describe non-normally distributed data. Two-way ANOVA (2 groups × 3 times) with repeated measures (for parametric variables) or the Kruskal–Wallis test (for non-parametric variables) will be used for the analysis of the TLT effects obtained in the three timelines: baseline, one week, and three weeks after the intervention. The Bonferroni correction for multiple comparisons will be employed as a post-hoc test. The effect size will be calculated based on the difference between means of the pre-intervention and post-intervention evaluations and will be expressed with respective 95% confidence intervals. Parametric Student’s t-test or a Mann–Whitney *U* test for non-parametric data will be employed to assess between-group (active and sham helmet) differences in age, height, weight, and body mass index (BMI), time of TBI injury, level of education, and Glasgow Coma Scale at admission on the emergency room. For all effects, a *p* value < 0.05 will be considered indicative of statistical significance. The data will be organized and tabulated using the Statistical Package for the Social Sciences (SPSSv.19.0).

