#### Neuropsychological assessment

Patients will be assessed at baseline, one week after the end of the LLLT, and three months after the LLLT sessions. Each patient will follow the participation period as shown in Fig. 1.

Instruments:Beck Depression Inventory (BDI-II), used to assess depressive symptoms, classified as minimal (0–11 scores), mild (12–19), moderate (20–35), and severe (36–63) [41, 42];Beck Anxiety Inventory (BAI), used to assess anxiety symptoms, classified as minimal (0–7 scores), mild (8–15), moderate (16–25), and severe (26–63) [42];Trail Making Test A and B (TMT A and TMT B), used to measure attention, speed, and mental flexibility. In TMT A, the patient is instructed to draw a line from 1 to 2, 2 to 3, and so on. In TMT B, the patient switches between numbers and letters, drawing a line from 1 to A, A to 2, 2 to B, and so on. On both forms A and B, the patients perform a sample before the real test. The patient is instructed to perform as fast as he/she can [43];Stroop Test - Version Victoria, measuring cognitive control with each person can maintain a goal in mind and suppress a habitual response in favor of a less familiar one. The interference effect is determining by calculating the extra time required to name colors (Card 3) in comparison to the time required to name colors in the control task (Card 1) [43, 44];Controlled Oral Word Association Test (COWAT), used to evaluate the spontaneous production of words under restricted search conditions (verbal association fluency). For the phonemic fluency task, the patient must provide orally as many words as possible beginning with the letters F, A, and S for 1 min for each letter. For the semantic fluency task, the patient is asked to produce as many animals’ names as possible within 1 min. The total correct is the sum of all admissible words for the semantic category [43];Five-point test, this test requires preproduction of novel designs under time constraints (3 min). The score is calculated including the total number of unique designs and the number of repeated designs (perseverations) [45];Symbol Digit Modalities Test (SDMT) oral version, the test is used to assess divided attention, visual scanning, tracking, and speed. The examiner records the numbers that correspond with symbols. The number of correct substitutions within the 90-s interval is the score of the task [46, 47];Rey Auditory Verbal Learning Test (RAVLT), measures immediate episodic memory, learning, susceptibility to interference, and recognition memory. A list of 15 nouns (list A) is read aloud to the patient, for five consecutive trials, each followed by a free-recall test. An interference list of 15 words (list B) is presented, followed by a free-recall test of that list. Immediately after this, delayed recall of list A is tested (Trial 6), and after 20 min (Trial 7), without further presentation of those words. The recognition is performed by presenting 50 words containing words from lists A, B, and new words, and the patient needs to identity the words from list A [43, 48];Sequence Numbers and Letters (Wechsler subscale - WAIS-III), used to evaluate working memory, random numbers, and letters is presented orally to the patient and must be mentally organized and immediately reported to the examiner with the following rule: first the crescent numbers then the letters (in alphabetical order). In test difficulty increases the patients correctly perform the task [49];Digit Span (DS) Forward and Backwards (WAIS-III), the DS assesses working memory. For the DS forward, the patient hears carefully a sequence of numbers and must repeat it immediately in the same sequence as previously presented. For the DS backwards, the patient must repeat the sequence inversely. In both conditions the number of numbers presented increases as the patient hits two corrects scores from the same span [49];Rey-Osterrieth Complex Figure Test (ROCF), the purpose is to assess visual–spatial constructional ability and visual memory. The patient is required to copy the ROCF, and after 3 and 30 min, a white sheet is given to the patient, and asked to draw the amount of information retained over time [50, 51].

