
### Primary outcome

Inhibitory attentional control (time score) measured by Stroop test. The Stroop test is known to be an accurate assessment of executive function in mild to moderate TBI [52].

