### Sample size

Based on the previous pilot study [37] that analyzed the cognitive function of patients with TBI after repetitive sessions of RED/Near-infrared LED treatment. Considering the improvement on Stroop test of 1 standard deviation (SD) related to the baseline, the level of significance of 0.05 and the power of 80%, 16 patients per group was estimated. Considering the rate of 15% of drop-outs, we added two participants per group, ending with a total sample of 36.

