## Discussion

The present study is designed to evaluate the effects of 18 sessions of LLLT over cognition, in patients with chronic moderate and severe TBI. Our primary hypothesis is that the sessions of active LLLT will improve attention (at least 1 SD) measured by Stroop test compared to the placebo group (sham LLLT). Our secondary hypothesis is that the active group will improve in all domains assessed by the neuropsychological battery, including cognition and mood, compared to placebo group.

LLLT can modulate many biological effects penetrating the scalp into the brain [25], playing a role improving the outcome of the patients in two different ways, depending on the stage of the trauma. In the acute phase after TBI, the initial neuronal injury occurs instantly and oftentimes causes irreversible damage to the central nervous system, due to impairment of neuronal cell functions, including mitochondria, and glia cells [18, 58]. The disruption of neuronal circuitry causes loss of connectivity between different areas of the brain and can negatively impact neural regeneration, leading to dysfunctional interactions. In the secondary stage after the trauma, other changes may occur, including release of neurotransmitters, decreased glucose utilization, lactic acid accumulation, reduced activity of ATP-reliant ion pumps, increased release of glutamate, Ca2 + −induced depolarization, and excitotoxicity [21, 58].

Previous studies showed improvement on cognition including attentional process and episodic memory after repetitive sessions of LLLT in patients with TBI [17, 37]. It seems that the LLLT decreases the inflammatory response, helping the neuroprotection after TBI. This process leads to increases on the ATP, cellular energy, and blood flow, decreasing the metabolic process. In summary, the LLLT seems to increase the intercellular synapses, acting as a possible treatment after acute and chronic TBI [37, 59–61].

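### Missing Stroop scores are to be imputed from four covariates, without treatment arm or the patient's own Stroop scores, which shrinks the estimated treatment effect by about the missing fraction

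*Protocol article*

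**What the plan says.** The primary outcome is "Inhibitory attentional control (time score) measured by Stroop test". On timing, the Neuropsychological assessment section states: "Patients will be assessed at baseline, one week after the end of the LLLT, and three months after the LLLT sessions". A patient who leaves after the first assessment therefore still has at least a baseline Stroop score.

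For missing values the Statistical analysis section says: "Missing data will be analyzed with regression imputation, considering the confounders (months of the trauma, years of age, schooling years, and depressive symptoms"). It also says "Intention-to-treat and per-protocol analyses will be performed for the primary and secondary outcomes", and the completed data go into a "Two-way ANOVA (2 groups × 3 times) with repeated measures (for parametric variables) or the Kruskal–Wallis test (for non-parametric variables"). The article mentions no multiple imputation, pooling, random residual or sensitivity analysis for missing data.

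The Sample size section plans for losses: "Considering the rate of 15% of drop-outs, we added two participants per group", which gives 18 per group. The Discussion states a between-group hypothesis: "active LLLT will improve attention (at least 1 SD) measured by Stroop test compared to the placebo group (sham LLLT").

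**The concern.** The article names the imputation method and lists what goes into it, so this is a choice it has made and not a detail left open. Arm is not in the list. A missing score in the active arm and one in the sham arm are then predicted from the same equation, and the imputed patients carry no treatment difference. They are nevertheless counted as observed in the ANOVA. The list also leaves out the patient's earlier Stroop scores, which would be expected to predict a missing Stroop score better than the four covariates do.

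At stake is the primary intention-to-treat comparison. The trial has little slack: it needs 16 per group and enrols 18, and 15% loss leaves 18 × 0.85 = 15.3. A rule that dilutes the difference at the planned drop-out works directly against the stated hypothesis.

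**Working it through.** **1. The plan's own figure.** Inputs from the Sample size section: "improvement on Stroop test of 1 standard deviation (SD) related to the baseline, the level of significance of 0.05 and the power of 80%, 16" per group. Taking the test as two-sided (the article does not say), n = 2 × (1.96 + 0.84)² / 1² = 15.7, so 16 per group. The stated figure is reproduced. The 1 SD difference, 18 per arm and 15% loss are therefore the natural inputs for the check.

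**2. Expected shrinkage.** Let δ be the true difference, μ the sham mean at follow-up, and m the fraction missing in each arm, with missingness unrelated to outcome. Arm is absent from the imputation model and baseline covariates are balanced by randomisation, so the expected imputed value is the same number c in both arms.

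- Active mean after imputation: (1 − m)(μ + δ) + m·c
- Sham mean after imputation: (1 − m)μ + m·c
- Difference: (1 − m)·δ

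With δ = 1 SD:

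- 15% missing: 0.85 SD
- 2 of 18 per arm: 16/18 = 0.89 SD
- 3 of 18 per arm: 15/18 = 0.83 SD
- 5 of 18 per arm: 13/18 = 0.72 SD

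This result does not depend on the covariates' R² or on the correlation between visits.

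Unequal losses give a similar answer. With 1 sham and 5 active patients missing, c lies 13/30 of the way from the sham mean to the active mean. The difference is 13/18 + (5/18 − 1/18) × 13/30 = 0.722 + 0.096 = 0.82 SD.

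**3. Coverage, power and type I error by simulation.** These need inputs that the article does not give. Assumed: the four covariates explain 15% of Stroop variance; baseline to follow-up correlation 0.6; one follow-up visit; change-score comparison; 18 per arm; 15% missing completely at random.

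| Method | Mean estimate (true 1 SD) | 95% CI coverage | Power | Type I error |
|---|---|---|---|---|
| As written: four covariates, single imputation | 0.85 | about 92% | 74–75% | about 5% |
| Complete cases, no imputation | about 1.00 | about 95% | about 84% | about 5% |

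At the planned drop-out, the stated imputation does worse than not imputing, by about 9 percentage points of power.

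**4. Sensitivity to the assumptions.** With R² 0.20 and 3 of 18 missing per arm, the estimate is 0.83–0.84 SD and coverage 91–93%. Change-score power is 67% against 76% for complete cases at correlation 0.5, and 83% against 93% at correlation 0.7. Across the settings run with R² 0.20, type I error under the method as written was 4.0–5.4%.

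**5. What a partial repair would do.** Suppose arm and baseline Stroop are added but each missing value is still filled once with its predicted value. The bias goes (estimate about 1.00 SD). Under the assumptions of step 3, however, the mean standard error is about 0.28 against a true sampling SD of 0.32–0.33, and type I error is about 9%.

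**6. What the full repair does.** Multiple imputation with arm and baseline Stroop, pooled by Rubin's rules (3 of 18 missing per arm, R² 0.20, correlation 0.7, change score), gives an estimate of 1.00 SD, mean SE 0.293 against an empirical 0.291, coverage 96% and power 90%. The method as written gives 0.84 SD, 92% and 83% in the same setting.

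**The case against.** The strongest objection concerns the reading. The bracket is introduced as a list of confounders. Arm and earlier Stroop scores are not confounders, so their absence does not prove that they are left out of the model. The text does not say single or deterministic either, and a condensed article may leave the full model to another document. This stands in part: both are plain readings and not explicit statements. But the method and its predictors are the only specification given, and an analyst who followed them would get the results above.

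Three stronger claims are tempting, and the document does not support them.

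- *The imputation inflates false positives.* As written it does not. The shrunken estimate and the shrunken standard error offset each other, and type I error stays near 5%. The 9% belongs to a partial repair that the article does not propose.
- *The intention-to-treat estimate is necessarily biased towards no effect by 15%.* That holds if missingness is unrelated to outcome and drop-outs would have had the full effect. If drop-outs stop sessions early and benefit less, the attenuation against an intention-to-treat target is smaller. Under informative drop-out both size and direction could differ. If 15% is the cumulative loss by the last visit, fewer are missing at one week and the shrinkage there is smaller.
- *Depressive symptoms will be missing at the same visits as Stroop.* That assumes the follow-up value is used. The other three predictors are baseline characteristics and the BDI-II is given at baseline, so the baseline value is at least as natural a reading. What stands is that the article does not say which visit it means.

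It is also fair that the simulation uses one follow-up and a change score, whereas the plan is a 2 × 3 repeated-measures ANOVA. The (1 − m) result still applies to the group difference at each visit; the power and coverage figures are indicative only.

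**Conclusion.** The point holds as a should-fix. Read plainly, the rule imputes outcomes without arm and without the patient's observed Stroop scores. With missingness unrelated to outcome and baseline covariates as predictors, it shrinks the expected between-arm difference by about the fraction missing at that visit, from 1 SD to about 0.85 SD at 15%. Under the assumptions of step 3, it lowers coverage to about 92% and power from about 84% to about 74–75%.

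The shrinkage follows by algebra from the omission of arm. Coverage and power rest on an assumed R² and correlation, and step 4 shows their range. The conclusion depends on taking the bracket as the full predictor list and on taking regression imputation in its ordinary single sense.

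**What to change.** Replace the imputation sentence with one of these:

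- **Multiple imputation**, at least 20 sets, with arm, all observed Stroop scores, months since trauma, age, schooling and baseline BDI-II in the model, results pooled by Rubin's rules. This is the smaller change.
- **A likelihood-based mixed model** on the observed Stroop scores with arm, visit and arm × visit. Baseline Stroop should be either a covariate, with post-baseline scores only as outcomes, or one of the modelled outcomes, but not both. This also replaces the planned ANOVA.

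Either way, change the predictors and the handling of imputation uncertainty together, for the reason in step 5. State that the depressive-symptom predictor is the baseline value. Since the shrinkage result assumes missingness unrelated to outcome, add a sensitivity analysis for data not missing at random.

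The cost is analysis wording and slightly more analysis work, with standard errors that reflect the missing data. No patient procedure changes. The Trial status section reports inclusion as ongoing, so the wording can be settled before any unblinded analysis.

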### Eligible participants

#### Inclusion criteria

Patients of both genders;Age range 18–60 years;Glasgow Coma Scale (GCS) ≤ 12 at admission in the emergency room;Computer tomography (CT) or magnetic resonance imaging (MRI) consistent with closed TBI, including intracranial hematoma, subdural hematoma, epidural hematoma, diffuse axonal injury, hemorrhagic contusion, and subarachnoid hemorrhage;Loss of consciousness ≥ 30 min;Post-traumatic amnesia of ≥ 24 h;Outpatients with > 6 months TBI;Signed informed consent.

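### The factors the protocol itself calls confounders are used only to impute missing data and are left out of the stated arm comparison, which costs precision and leaves a 36-patient trial exposed to chance imbalance

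*Protocol article*

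**What the plan says.** All references are to the protocol article.

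- **Statistical analysis, first paragraph.** Missing values are to be filled in by regression, "considering the confounders (months of the trauma, years of age, schooling years, and depressive symptoms". This is the only use given for the four factors under the name of confounders.
- **Statistical analysis, second paragraph.** The treatment effect is to be analysed by "Two-way ANOVA (2 groups × 3 times) with repeated measures (for parametric variables) or the Kruskal–Wallis test (for non-parametric variables". No covariate is named for either method.
- **Statistical analysis, baseline comparison.** t-tests or Mann–Whitney tests "will be employed to assess between-group (active and sham helmet) differences in age, height, weight, and body mass index (BMI), time of TBI injury". The list goes on to schooling and the admission coma score. Depressive symptoms are not listed. No action is attached to the results.
- **Randomization.** Patients are "randomly divided into two groups with a 1:1 ratio and blocks of four and six". No stratification is stated.
- **Inclusion criteria.** "Age range 18–60 years" and "Outpatients with > 6 months TBI", so age and time since injury can both vary widely.

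**The concern.** The plan judges four variables important enough to predict a missing Stroop score, yet leaves them out of the model for the observed scores. Blocking of the stated kind balances numbers per arm, not these factors. What remains for three of them is a significance test at baseline. In a properly randomised trial such a test asks a question whose answer is already known, and at this size it flags only large differences.

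Two things are at stake. The first is precision: any part of the change in Stroop time that these factors explain stays in the error term. The second is chance imbalance: if the arms differ by luck on a factor that predicts recovery or practice gain, the unadjusted estimate in this one trial carries that difference, and nothing in the stated analysis removes it. If a covariate is added only after the data are seen, the choice is open to question. If it is fixed beforehand, it is not.

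**Working it through.** **Inputs from the protocol article.** Target effect 1 SD on the Stroop test, alpha 0.05, power 80%, 16 per group, 36 in total, hence 18 per arm (Sample size). Alpha is taken as two-sided, because the article does not say. Correlations and R² are assumptions, because the article gives none.

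**The plan's own figure.** n per arm = 2 × (1.96 + 0.84)² / 1² = 15.7, rounded up to 16. This matches the stated 16. Results are shown at 18 per arm (all randomised) and 16 per arm (the estimated requirement).

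**1. How large chance imbalance can be.** The SD of a standardised difference in means between arms is √(2/n).
- n = 18: √(2/18) = 0.333, so P(|imbalance| > 0.5 SD) = 2 × [1 − Φ(0.5/0.333)] = 0.134.
- n = 16: √(2/16) = 0.354, so the probability is 0.157.
- If the factors are independent, the chance of at least one such imbalance at 18 per arm is 1 − (1 − 0.134)³ = 0.35 for three factors and 0.44 for four.

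**2. What the baseline tests can see.** The smallest significant imbalance is t(0.975; 2n − 2) × √(2/n).
- n = 18: 2.032 × 0.333 = 0.68 SD.
- n = 16: 2.042 × 0.354 = 0.72 SD.
- In a simulation of 200,000 trials at 18 per arm, about 63% of observed imbalances of 0.5 SD or more were non-significant.

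**3. Effect on the arm difference.** The treatment effect in a repeated-measures ANOVA that includes baseline is the group-by-time interaction, so the relevant r is the correlation of the factor with change in Stroop. The shift is r × imbalance, in SDs of change. The conditional type I error uses the nominal standard error and a residual SD of √(1 − r²), at 18 per arm.

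| r (assumed) | Shift at 0.5 SD imbalance | Type I error given that imbalance |
|---|---|---|
| 0.2 | 0.10 SD | 5.6% |
| 0.3 | 0.15 SD | 6.2% |
| 0.5 | 0.25 SD | 8.2% |

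Over all randomisations the error rate stays at 5%.

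**4. What adjustment gains and costs.** With k covariates, the variance of the arm difference is multiplied by (1 − R²) × (N − 3)/(N − k − 3).
- k = 4, N = 36: 33/29 = 1.14, break-even R² = 1 − 29/33 = 0.12.
- k = 4, N = 32: 29/25 = 1.16, break-even R² = 1 − 25/29 = 0.14.
- k = 2, N = 36: 33/31 = 1.06, break-even R² = 1 − 31/33 = 0.06.

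Power for 1 SD at 18 per arm (normal approximation) is 85% unadjusted. With four covariates and the penalty included:

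| Joint R² (assumed) | Variance multiplier | Power |
|---|---|---|
| 0.10 | 0.90 × 1.138 = 1.02 | 84% |
| 0.20 | 0.80 × 1.138 = 0.91 | 88% |
| 0.30 | 0.70 × 1.138 = 0.80 | 92% |

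**The case against.** The strongest reply is that nothing here is a statistical error. In a randomised trial these are prognostic factors, and chance imbalance is already allowed for in the 5% error rate and in the confidence interval. That stands, and it limits the point to precision and to imbalance in the trial actually drawn.

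A second reply is that an ANOVA with baseline among its time points cancels any stable effect of schooling or age on Stroop level. That also stands. Only effects on change remain, so the realistic correlations may lie at the low end of the range above. The Kruskal–Wallis alternative, if applied to raw scores at each visit, would not have this protection.

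A third reply is that covariates are often left to an analysis plan. This carries less weight. The article names the factors and fixes the method in adjoining paragraphs without joining them, so the comment concerns a stated method and not absent detail.

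A reader might infer three stronger charges, and the document supports none of them:

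- **That the trial relies on the baseline tests as proof of balance.** The section lists them beside height, weight and BMI and ties no decision to them.
- **That the open upper limit on time since injury is a design fault.** It contradicts nothing in the article. It only widens the spread of a factor that the article calls a confounder, and the article gives no recovery time course from which to separate patients still recovering from those at a plateau.
- **That imbalance will be mistaken for a treatment effect.** It may shift one trial's estimate, but it does not bias the procedure.

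**Conclusion.** The point holds as an avoidable weakness in a stated analysis. The protocol's own prognostic factors are left out of the comparison they bear on, and the baseline tests are no substitute: an imbalance of 0.5 SD has a 13% chance per factor at 18 per arm, and the tests respond only from 0.68 SD. The unadjusted analysis remains valid.

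The consequence is moderate. The shift is 0.10 to 0.25 SD of change for a 0.5 SD imbalance, against a target effect of 1 SD. The change in power with all four factors runs from about −1 to +7 percentage points for joint R² of 0.10 to 0.30. Both ranges rest on assumed correlations with change in Stroop, two-sided alpha and, for the chance of at least one imbalance, independent factors.

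**What to change.** 1. Pre-specify the between-arm comparison of the Stroop time score as an ANCOVA or a mixed model for the post-treatment scores, with baseline Stroop as the first covariate.
2. Add a short, fixed set of the named factors: months since trauma (on a log scale if skewed), age and schooling years. If depressive symptoms are included, use only the baseline score, because later scores are themselves a secondary outcome. Keep the set whatever the baseline data show.
3. Deal with non-normality inside that model, by transforming or ranking the outcome, instead of switching to an unadjusted Kruskal–Wallis test.
4. Report baseline characteristics by arm descriptively, including depressive symptoms, without p values.

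**Cost.** The change is to wording only. The article already plans to record all of these variables, and no more patients are needed. The Trial status section accounts for 12 + 4 + 2 = 18 of 36 patients, so on the article's own account the set could be fixed before the analysis. Each covariate takes about one of 34 degrees of freedom. Four weak covariates would lose precision: at a joint R² of 0.09 the variance rises by about 4% at N = 36 (0.91 × 33/29 = 1.04). Baseline Stroop and one or two of the named factors would therefore be safer than all of them.

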**Fig. 3 Fig3:**
[figure not shown]
**a** Two identical helmets, active and sham stimulation. **b** The inside view of the active LLLT helmet

The rationale follows: optimal wavelength penetration within biological tissues, occurs with a wavelength range of 600–1000 nm [40]. The inactive helmet (sham) contains only LEDs with power < 1 mW, only serving to simulate the irradiation of the patient. All the patients will be submitted to 18 30-min LLLT sessions (active or sham condition), three times per week over six weeks. For safety, after the LLLT intervention, the patient will be asked about side effects between sessions.

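### As worded, the 60% adherence rule puts non-adherent patients into the per-protocol set instead of leaving them out

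*Protocol article*

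**What the plan says.** The Statistical analysis section of the protocol article opens by planning two analyses: "Intention-to-treat and per-protocol analyses will be performed for the primary and secondary outcomes". After a sentence on missing data, it gives its only rule on adherence: "Patients that did not receive 60% of the total stimulation will be considered non-adherent and analyzed as per-protocol".

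The treatment course to which the 60% applies is in the LLLT intervention section: "All the patients will be submitted to 18 30-min LLLT sessions (active or sham condition), three times per week over six weeks".

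No other section says who belongs to the per-protocol set, and none says that non-adherent patients are left out of it.

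**The concern.** A per-protocol analysis is restricted to patients who followed the planned treatment closely enough, so that it can say something about the effect of treatment actually received. Here the patients below the threshold are named as non-adherent and, in the same clause, assigned to that analysis. The destination is the reverse of what the term means.

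This differs from a definition left to a fuller document. The article states a rule, with a numerical threshold and a place for the patients, and the place is wrong. An analysis plan that followed the sentence would carry the error forward, and one that departed from it would contradict the published protocol. At stake is the meaning of the per-protocol result, which is planned for the primary outcome as well as the secondary ones.

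**Working it through.** **1. The plan's own figure.** The only related number that can be reproduced is the sample size. The Sample size section assumes "Considering the improvement on Stroop test of 1 standard deviation (SD) related to the baseline" and continues: "the level of significance of 0.05 and the power of 80%, 16 patients per group was estimated". Taking the test as two-sided (the article does not say) and using the normal approximation with a difference of 1 SD:

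n per group = 2 × (1.96 + 0.84)² / 1² = 15.7, rounded up to 16.

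This matches. The figure is background only, since nothing in this point depends on it.

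**2. Where the threshold falls.** Planned sessions: 18. Threshold: 60%.

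- 0.60 × 18 = 10.8 sessions
- 10/18 = 55.6%, below the threshold
- 11/18 = 61.1%, above the threshold

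Counted by sessions, a non-adherent patient has 10 or fewer and an adherent patient has 11 or more. The article does not say whether stimulation is counted in sessions, minutes or delivered dose. Counting minutes of complete 30-minute sessions gives the same cut (0.60 × 18 × 30 = 324 minutes; 324/30 = 10.8). Sessions cut short could move a patient across it.

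**3. What the sentence yields under each reading.**

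- *The per-protocol set is the non-adherers.* The comparison is made only among patients with 10 or fewer sessions.
- *The per-protocol set includes the non-adherers along with everyone else.* Nobody is removed for non-adherence, so the set does not differ on that ground from all randomised patients.
- *Non-adherers are dealt with through the per-protocol analysis, by being excluded from it.* The set holds patients with 11 or more sessions. This is a usual per-protocol set, but the words do not say it.

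Only the third gives an estimate of the effect of adequate treatment.

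**4. How many patients could be involved.** The article gives no expected rate of non-adherence. The nearest figure is the drop-out allowance: "Considering the rate of 15% of drop-outs, we added two participants per group, ending with a total sample of 36". Drop-out and non-adherence are different events, so this serves only to set an assumed range, from half to twice the allowance:

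| Assumed non-adherence | Below 60%, of 36 | At or above 60%, of 36 |
|---|---|---|
| 7.5% | 0.075 × 36 = 2.7 | 33.3 |
| 15% | 0.15 × 36 = 5.4 | 30.6 |
| 30% | 0.30 × 36 = 10.8 | 25.2 |

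On these assumptions the first reading would leave about 3 to 11 patients across both arms, against about 25 to 33 under the third.

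**The case against.** The strongest reply is that this is a slip of wording and not an inverted plan. The article's English is loose in other places, the sentence itself calls these patients non-adherent, and a 60% cut-off has no use unless it separates adherers from non-adherers. Nobody is likely to run a comparison on the non-adherers alone. This stands as an account of what was probably meant, and it lowers the weight of the point. It does not remove the point, because the text as published says otherwise and no other section corrects it.

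Three stronger inferences are tempting, and the document does not support them:

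- *Non-adherers leave the intention-to-treat analysis, so the primary result is open to selection bias.* A reader might take the sentence to mean per-protocol in place of intention-to-treat. But the section plans an intention-to-treat analysis for the primary and secondary outcomes, and nothing in it takes any randomised patient out of that analysis.
- *The plan is defective because it does not say which analysis decides the primary hypothesis.* That is an omission of a kind commonly left to a fuller protocol or an analysis plan, neither of which is shown. It is also a separate matter from the faulty rule.
- *About 5 of 36 patients would form the per-protocol group.* That number treats the drop-out allowance as if it were the non-adherence rate. A patient can complete all sessions and miss the follow-up, or miss sessions and still be assessed. Only an assumed range can be given.

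**Conclusion.** The sentence is wrong as written. It places patients below 60% of the stimulation in the per-protocol analysis, and the article contains no other definition of that set. Applied literally, the per-protocol analysis of the primary and secondary outcomes would consist of, or include, the non-adherers and would not estimate the effect of adequate treatment.

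The consequence stops there: the randomised comparison by intention-to-treat stands and no sample-size figure changes. Exclusion was probably intended. The point is therefore a definite correction to a stated rule, but not one on which the validity of the trial's main comparison depends. The cut between 10 and 11 sessions assumes that stimulation is counted by sessions, and the count of affected patients (about 3 to 11 of 36) rests wholly on the assumed range of 7.5% to 30%.

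**What to change.** Replace the sentence with wording such as:

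> Patients who received less than 60% of the total stimulation (fewer than 11 of 18 sessions, if counted by sessions) are considered non-adherent; they remain in the intention-to-treat analysis in their randomised arm and are excluded from the per-protocol analysis.

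The sponsor should confirm that sessions are the intended unit and, if an analysis plan exists, make it agree. The change keeps the sponsor's own threshold, adds no patients and alters nothing in the treatment or the visits. It costs one sentence. The Trial status section describes inclusion as ongoing, so as of this article it could be made before the final analysis.
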